# Evaluation of a hospital-based day-structuring exercise programme on exacerbated behavioural and psychological symptoms in dementia - the exercise carrousel: study protocol for a randomised controlled trial

**DOI:** 10.1186/s13063-015-0758-2

**Published:** 2015-05-26

**Keywords:** Dementia, RCT, Old age psychiatry, Exercise, BPSD, Circadian rhythms, Rest-activity-cycles, Body-fixed motion sensors

## Abstract

**Background:**

Conceptual reviews and observational studies describe a link between physical inactivity and behavioural disturbances in people with dementia. Consequently, treatment of these symptoms requires physical activation and pharmacological or physical immobilization should be avoided. The few trials that have been conducted in inpatient dementia care to investigate the effects of exercise on behavioural and psychological symptoms revealed inconsistent results. Due to a lack of evidence, there is a paucity of recommendations for physical activation in this stage of care. Therefore, this trial seeks to investigate the effects of a day-structuring exercise programme on behavioural and psychological symptoms as well as on circadian rhythms of patients with dementia, hospitalized because of their behavioural and psychological disturbances.

**Methods/Design:**

A single-centre randomised controlled trial will be conducted in three special dementia care units of an old age psychiatry hospital. Enrolled patients will receive either a 2-week exercise programme, or a 2-week social stimulation programme in addition to usual care. Due to the provision of four day-structuring exercise-sessions in the course of an intervention day, the exercise programme for the study group is called *exercise-carrousel*. Baseline and post-intervention assessment for the primary outcome variable - the overall effects on behavioural and psychological symptoms - will be measured by the Alzheimer's disease Cooperative Study-Clinical Global Impression of Change. The following objectives are set up as secondary outcomes: dimensions of the behavioural and psychological symptoms of dementia (BPSD) and caregiver burden, routine and on-demand psychotropic medication, patients’ motor behaviour, diurnal cortisol-levels from saliva probes and brain-derived neurotrophic factor-levels from blood serum.

**Discussion:**

In order to be regarded as an important treatment option for behavioural and psychological symptoms, physical activation in inpatient hospital dementia care requires more evidence and appropriate recommendations. Respecting hospital routines and the intra-daily variability of the patients’ motivation and behavioural disturbances in the provision of exercise sessions could lead to higher exercise adherence and better effects on patients’ behavioural and psychological symptoms than former trials have presented. The concealment of allocation throughout the trial and the rating of individual exercise exertion present the key challenges and main limitations of this trial.

**Trial registration:**

DRKS00006740 (German Clinical Trial Register, date of registration: 28 October 2014).

## Background

The treatment of behavioural and psychological symptoms of dementia (BPSD) is a key challenge in inpatient dementia care [1, 2]. During the course of the disease nearly every patient suffers from an exacerbation of behavioural and psychological symptoms. Due to extreme caregiver and environmental burden, such phases often lead to admission into specialised Dementia Care Units (DCU) in old age psychiatric departments.

The application of antipsychotic medication is a standard treatment method for behavioural disturbances in inpatient dementia care. Owing to potential side effects of neuroleptics [3], clinicians seek non-pharmacological approaches for the treatment of BPSD [4]. A conceptual review [5] and an observational, cross-sectional trial [6] describe a direct link between physical inactivity and increased behavioural disturbances. Considering these findings, more physical activation in DCU is recommended, possibly leading to a reduced use of sedative medication and physical constraints. This non-pharmacological approach shows the positive effects of physical activation and may help to reduce critical side-effects of psychopharmacotherapy.

Unlike the good evidence for exercise as a key-factor in the prevention of dementia [7–9], research focussing on the effects of exercise in dementia care is in its ‘infancy’ [10]. While exercise trials focussing on functional performance and activities of daily living show promising results [11, 12], there is a paucity of clinical trials investigating the effects of exercise on BPSD. While trials in long-term nursing home care reveal promising effects on some BPSD - especially on mood, agitation and circadian disturbances - there are only a few clinical studies in inpatient hospital dementia care with consistent results [13]. The Cochrane Review by Forbes *et al.* [11] includes only one trial investigating the effects of exercise on BPSD [14]. This 1-year nursing-home exercise trial, conducted with an overall participation-rate of 30 %, showed no effects on BPSD [14]. As the low level of participation and consequently low level of physical activation could be a determining factor explaining only minimal effects on BPSD, future research should focus on approaches with better exercise adherence and higher levels of physical activation [6].

In addition to physical activation, the organisation of non-pharmacological treatment in the course of a day is a key component of inpatient dementia care [15]. Disease-related changes in circadian motor behaviour, that is, wandering, agitation or sundowning, affect almost every patient in advanced stages of dementia [16]. In this context, sundowning is denoted as an increase of BPSD in the late afternoon and early evening hours. As a low level of daytime activity is linked to a higher fragmentation of circadian rest-activity cycles [17], structured exercise programmes may help to synchronise and reduce circadian rhythm disturbances [16, 18].

Taking into account the assumed positive effects of physical exercise on BPSD and the necessity of providing day structure through activities in dementia care, our research group has conducted a pilot study. The aim of this pilot study was to investigate the feasibility of the planned day-structuring physical activation programme in a hospital setting. Eighteen patients suffering from acute exacerbation of behavioural symptoms in dementia were included. These patients received a 2-week complex day-structuring exercise programme in addition to their usual treatment - the same intervention as planned for the randomised controlled trial (RCT). Two thirds of these patients accomplished more than 180 minutes of exercise per week. In this pilot-study we found reductions in some BPSD; furthermore we found stabilisation of day-structure and a decrease in caregiver burden. Based on these preliminary findings, our planned RCT trial aims to investigate the effects of a day-structuring exercise programme in inpatient hospital dementia care.

### Objectives

The primary objective of this trial is to investigate the effects of a day-structuring exercise programme on BPSD in inpatient hospital dementia care. The promising results of our pilot-study regarding the feasibility and effects of the *exercise-carrousel* on BPSD in hospital old age psychiatry care, led to the following study-hypothesis:*The intervention group, carrying out a 2-day-structuring exercise intervention in addition to treatment as usual (TAU), is hypothesized to show reduced BPSD at follow-up. In contrast, the control group, receiving social stimulation in addition to TAU, is not expected to show such changes.*

In addition to investigating the putative effects of the day-structuring exercise on BPSD, the following secondary-endpoint parameters are investigated: caregiver burden, total dose and frequency of application of antipsychotic and sedative medication, circadian rhythms of motor behaviour, saliva cortisol-levels and brain-derived neurotrophic factor.

## Methods/Design

### Design

An RCT with pre- and post-intervention-assessment (Fig. 1) will be conducted in the department of old age psychiatry at the LVR-Hospital Cologne, an academic teaching hospital of the University of Cologne. All assessors of eligibility criteria and outcome measurements will be blinded to group allocation. Ethical approval was obtained by the Ethics Commission of the German Sport University Cologne and the Ethics Commission of the North-Rhine Medical Chamber (reference number: 2014216). This trial is registered in the German National Register of Clinical Trials (DRKS00006740).

**Fig. 1 Fig1:**
[figure not shown]
Trial flow chart

### Sample

Patients from three special DCU of the LVR-Hospital Cologne will be screened by two senior psychiatrists, who are not part of the study team, based on the following inclusion criteria: diagnosis of dementia according to ICD-10-criteria [19] and a minimum length of stay of one week before enrolment into the study, in order to help patients get familiarised to the new ward setting and to exclude delirium. Clinical exclusion of delirium is furthermore based on the validated German version of the Confusion-Assessment-Method, which is performed in all eligible patients [20, 21]. Patients must be able to perform the Timed Up and Go Test (TuG) [22]. Written consent of the patients’ legal guardian as well as from the patient is required. Patients will be excluded according to the following criteria: symptomatic, non-vascular or non-neurodegenerative dementia, no legal guardian, cardiac diseases denying exercise participation; and aggressive behaviour that prevents participation in groups.

### Sample size

The calculation of the sample size was performed via G*Power 3.1 [23], taking into account following parameters: a medium effect size (d = 0.5) for the primary objectives, the overall effects on BPSD measured by the Alzheimer’s Disease Cooperative Study-Clinical Global Impression of Change (ADCS-CGIC) [24, 25], from our pilot-study; a 1:1 allocation rate; two measurements; non-parametric analysis due to ordinal characteristics of the instruments assessing the primary objective; and an α-error of 0.05 and a power of 0.80 (1-ß-error) according to Cohen [26]. Based on this calculation, each group shall include 53 patients. The enrolment of 130 patients is planned, as a drop-out rate of 25 % is expected based on the experience from the pilot study.

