#### Outcome measures

All outcome measurements will be conducted by experienced assessors from nursing and medical staff, blinded to group allocation. Primary and secondary outcome variables are presented in Table 1.

**Table 1 Tab1:** Objectives and instrumental set-up of the trial

	Variable	Instrument
Primary objective	Behavioural and psychological symptoms (BPSD)	Alzheimer’s Disease Cooperative Study-Clinical Global Impression of Change [33]
Secondary objective	Dimensions of BPSD	Neuropsychiatric Inventory (NPI) [35]
		Cohen-Mansfield-Agitation-Inventory [36]
	Caregiver burden	NPI-caregiver-subscale [35]
	Application of antipsychotics	Chlorpromazine-equivalents [34]
	Application of benzodiazepine	Diazepam-equivalents [36]
	Motor behaviour	Body fixed motion sensor
	Saliva cortisol levels	Demeditec™ saliva kits [42]
	Neurotrophic factor levels	Brain-derived neurotrophic factor from blood-serum probes [44]

As the overall effect of our intervention on BPSD as rated by the ADCS-CGIC [24, 25] is the primary outcome, that is the measure on which we will focus.

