#### Analysis

The patients’ baseline characteristics in both groups will be compared via Chi-square test for categorical data, Wilcoxon rank test for non-parametric or non-normally distributed characteristics and *T*-test for continuous and normally distributed characteristics. Pre-post-outcome analysis within and between the groups will be realised per intention-to-treat analysis for the primary outcome variable via Friedman analysis of variance (ordinal characteristics) and analysis of variance for interval characteristics. The analysis of circadian rhythms in motor behaviour will be conducted according to Witting *et al.* [45] by calculating inter-daily stability, intra-daily variability and relative amplitude. Advanced time series analysis of the patients’ daily activity patterns will be developed in accordance with recent developments by Kirste *et al.* [46]. Analysis of the patients’ characteristics and outcome criteria will be realised using SPSS (version 22) and Matlab (version R2014b).

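### Friedman analysis of variance, the only test named for the ordinal primary outcome, has no treatment-arm term and cannot test exercise against control

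*Protocol article*

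**What the plan says.** Table 1 under Outcome measures names the primary instrument as the Alzheimer's Disease "Cooperative Study-Clinical Global Impression of Change" (ADCS-CGIC). The Abstract (Methods/Design) plans "Baseline and post-intervention assessment for the primary outcome variable".

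The Sample size section uses "a medium effect size (d = 0.5) for the primary objectives", 1:1 allocation, α = 0.05, power 0.80 and "two measurements; non-parametric analysis due to ordinal characteristics of the instruments assessing the primary objective". It concludes that "each group shall include 53 patients". It names neither the test nor its sidedness.

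The Analysis section plans an intention-to-treat pre-post comparison, inside each arm and across arms, "for the primary outcome variable via Friedman analysis of variance (ordinal characteristics"). Ordinary analysis of variance is reserved for interval-scaled variables. No other procedure is given for the ordinal primary outcome.

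The Objectives section states the hypothesis: BPSD fall in the exercise arm, and no such change is expected in the social-stimulation arm.

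**The concern.** The trial asks whether exercise does better than social stimulation. Friedman's test ranks repeated values within each patient and asks whether the time points differ. Treatment arm does not enter it. The Analysis section therefore promises a comparison across arms and names a method that cannot make one.

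This matters here because patients are admitted for exacerbated symptoms and all receive usual care, so improvement over two weeks in both arms is plausible. A test of time would pick up that improvement and could be reported as an effect of exercise.

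The instrument adds an ambiguity. It is named an impression of change, and the article does not say what, if anything, is scored at T0. If only the post-intervention change rating exists, there is no pair of values to rank.

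**Working it through.** **1. Reproducing the plan's 53 per group.**

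Inputs from Sample size: d = 0.5, α = 0.05, power 0.80, 1:1. Assumed, because not stated: a two-group Wilcoxon rank-sum test on one value per patient, with normal-parent efficiency 3/π.

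- Effective n per group = 53 × 3/π = 50.6; noncentrality = 0.5 × √(50.6/2) = 2.52; df = 2 × 50.6 − 2 = 99.2.
- One-sided: critical t = 1.66, power 0.803. With 52 per group power is 0.796, so 53 is the smallest n that reaches 80%.
- Two-sided: critical t = 1.98, power 0.702. Reaching 80% takes 67 per group (0.801).

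So 53 matches a one-sided between-arm rank test on one value per patient. The two-measurements input is not needed to reach it. A one-sided rank test on change scores also gives about 53, but only at a pre-post correlation of 0.5, where the SD of change equals the SD of a single value. Both are between-arm tests; neither is Friedman.

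**2. What Friedman does with these data.**

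*One change rating per patient.* There are no repeated values to rank, so the statistic does not exist.

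*Two values per patient.* With two time points and ties allowed for, the statistic is

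χ² = (B − W)² / (B + W), on 1 df,

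where B and W are the numbers of patients better and worse. Arm does not appear.

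**3. Behaviour when exercise has no effect.**

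The response splits below are assumptions, identical in both arms. At expected counts with 50% better, 30% same, 20% worse and n = 53: B = 26.5, W = 10.6, χ² = 15.9²/37.1 = 6.8, against a critical value of 3.84. Summing over the binomial distributions gives the share of trials with p < 0.05:

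| Better/same/worse, both arms | One arm, n = 53 | Pooled, n = 106 |
|---|---|---|
| 50/30/20 | 76% | 97% |
| 40/35/25 | 27% | 49% |
| 30/40/30 (no net change) | 5% | 5% |

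The test holds its 5% level only when there is no net change over time.

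**4. Running Friedman separately in each arm.**

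This is one way to read a combined within-arm and between-arm analysis, and it mirrors the wording of the hypothesis. With no exercise effect, the chance that the exercise arm is significant and the control arm is not is 0.76 × 0.24 ≈ 0.18 under 50/30/20, and 0.27 × 0.73 ≈ 0.20 under 40/35/25. Setting two within-arm p-values side by side is not a 5% test of the difference.

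**5. Check under a different model.**

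Simulated seven-level scores, 53 per arm, pre-post correlation 0.5 before rounding, both arms improving by 0.5 SD: Friedman rejected in 99% of runs pooled and about 86% within each arm. A two-sided rank test of change between the arms rejected in 4%.

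**The case against.** The strongest defence is that between-arm intent is clear. The Analysis section says the arms will be compared by intention to treat, the Objectives state a comparative hypothesis, and a fuller plan may hold the between-arm procedure. The intent is not in doubt. But this is not a detail left to another document: the article names a method for the primary outcome, and that method does not do what the same sentence promises. A later plan may correct it before the data are seen, so it does not follow that the test would have to be chosen after the results are in.

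Several stronger readings are tempting and are not supported.

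- *The ADCS-CGIC is scored only once, so the Abstract and the Sample size section are wrong.* The single score is an inference from the instrument's name; the article gives no scoring rule. A baseline assessment is compatible with a reference interview against which change is later judged, and the two-measurements input can be read in the same way.
- *The two-measurements input made 53 wrong.* No numerical effect can be shown. The figure is reproduced without it.
- *T0 is rated as change since admission, so a T1 minus T0 comparison loses power.* Nothing in the article suggests such a rating, so no loss can be attributed to it.

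The percentages in the table also rest on assumed splits and are not forecasts. The absence of an arm term does not depend on them.

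**Conclusion.** The point stands for the test named in the Analysis section. Followed as written, Friedman either cannot be computed (one rating) or tests change over time in patients (two values). Neither tests exercise against control, whatever is scored at T0.

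How often it would mislead depends on the improvement common to both arms: about 27% to 76% of trials within an arm of 53, and 49% to 97% pooled, under the two assumed splits with net improvement; 5% if there is none.

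The 53 per group is not shown to be wrong. It fits a one-sided between-arm rank test, which is not the test named. That attribution is itself an inference, since the article states neither test nor sidedness. If the replacement test is two-sided, power at d = 0.5 is about 70%.

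**What to change.** In Analysis, replace Friedman for the primary outcome with a between-arm comparison of the post-intervention ADCS-CGIC change rating in all randomised patients: a two-sample Wilcoxon rank-sum test, or a proportional-odds model that includes the minimisation factors. The choice between these is a preference; the between-arm comparison is what matters. State that T0 serves as the reference assessment for that rating. In Sample size, name the same test and clarify or drop the two-measurements input.

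State the sidedness and the power that goes with it: 80% at 53 per group one-sided, about 70% two-sided.

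The change itself is wording only, with no new visits or measurements. The cost is that the stated power becomes less favourable if the test is two-sided. Restoring 80% would then be a separate decision: 67 per group, 134 analysed, or 134/0.75 = 179 enrolled at the plan's own 25% drop-out, against the 130 planned.

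### From the stated inputs, 53 per group is exactly what a one-sided 5% rank-sum test requires, but no one-sided test is declared; at two-sided 5% the power is about 70%, not 80%

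*Protocol article*

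**What the plan says.** The Sample size section of the protocol article says "The calculation of the sample size was performed via G*Power 3.1". The effect assumed is "a medium effect size (d = 0.5) for the primary objectives", attributed to the pilot study. Groups are of equal size and each patient is measured twice. The type of test is described only as "non-parametric analysis due to ordinal characteristics of the instruments assessing the primary objective". The error rates are given as "an α-error of 0.05 and a power of 0.80". The result is "Based on this calculation, each group shall include 53 patients". The section does not name the test chosen in the software, the number of tails or a pre-post correlation.

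The Analysis section plans pre-post comparisons within and between groups, by intention to treat, for the primary outcome "via Friedman analysis of variance (ordinal characteristics) and analysis of variance for interval characteristics". It gives no sidedness either. The hypothesis under Objectives is worded in one direction (symptoms fall with exercise and do not change in this way in controls), but it is not tied to a one-sided test.

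**The concern.** A sample size is tied to the test and error rate behind it. Here α is printed without sidedness, and the tests named later reject in either direction. A reader will therefore take 0.05 as two-sided and 0.80 as the power at that level. If the number came from a one-sided calculation, that reading is wrong.

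The consequence depends on which level was meant:

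- **Two-sided 5%.** The chance of missing an effect of d = 0.5 is nearer 30% than the stated 20%, which matters when a null result is read.
- **One-sided 5%.** The false-positive rate in the favourable direction is 5%, twice the 2.5% that a two-sided 5% test allows, and the reader is not told.

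**Working it through.** **Inputs** (all from Sample size): d = 0.5; equal groups; α = 0.05; power = 0.80; non-parametric analysis. **Assumptions made here:** the test is the two-group Wilcoxon-Mann-Whitney test, and the parent distribution is normal, so the asymptotic relative efficiency (ARE) to the t-test is 3/π = 0.955.

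**Formula.** With n per group, use a noncentral t distribution with noncentrality δ = d·√(n·ARE/2) and df = 2·n·ARE − 2. Power is the probability of passing the one- or two-sided 5% critical value.

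**Step 1: reproduce 53.**

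- n = 53: n·ARE = 53 × 0.955 = 50.61; δ = 0.5 × √(50.61/2) = 2.515; df = 99.2.
- One-sided critical value 1.660: power **0.803**. At n = 52 the power is 0.796, so 53 is the smallest n that reaches 0.80.

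**Step 2: same n, two-sided.**

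- Critical value 1.984: power **0.702**.
- A simulation of the Mann-Whitney test (20,000 runs, normal data, 53 per group) gave 0.802 one-sided and 0.699 two-sided.

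**Step 3: what two-sided 5% would need.**

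- n = 66 gives 0.795 and n = 67 gives 0.801, so **67 per group**.
- With 53 per group, two-sided power reaches 0.80 at d = **0.56**.

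**Step 4: other two-group calculations.** Patients per group for 80% power at d = 0.5:

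| Calculation | One-sided | Two-sided |
|---|---|---|
| Rank-sum, normal parent | 53 | 67 |
| t-test | 51 | 64 |
| Normal approximation | 50 | 63 |
| Rank-sum, logistic parent | 46 | 59 |
| Rank-sum, minimum ARE (0.864) | 59 | 74 |
| Rank-sum, Laplace parent | 34 | 43 |

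Only the one-sided rank-sum calculation with normal parent gives 53. No two-sided entry is within 2 of it.

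**Step 5: routes that use the two measurements.** These need a pre-post correlation ρ, which the article does not give, so a range is shown.

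- *Repeated-measures analysis of variance, between-group F test.* With f = d/2 = 0.25, λ = N·f²·2/(1 + ρ). For ρ = 0.5, 0.6, 0.65 and 0.7 the need is 49, 52, 53 and 55 per group. At ρ = 0.65 and N = 106, λ = 106 × 0.0625 × 2/1.65 = 8.03 and power is 0.802.
- *Repeated-measures group-by-time interaction.* With f = 0.25, λ = N·f²·2/(1 − ρ). The need is 33 per group at ρ = 0 and 17 at ρ = 0.5, well below 53.
- *Baseline-adjusted two-sided rank comparison.* Multiplying n by ARE/(1 − ρ²) gives 61, 57, 55, 51 and 43 per group at ρ = 0.3, 0.4, 0.42, 0.5 and 0.6.

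**Step 6: compare with the named analysis.** The Friedman statistic is referred to chi-square and the analysis of variance to F. For a two-group or two-time comparison, either at 0.05 corresponds to a two-sided 5% test. The one-sided 5% level that yields 53 in Step 1 is therefore not the level at which the named tests operate.

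**The case against.** Three objections carry weight.

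**The article lists two measurements as an input.** A plain rank-sum calculation has no such input. A reader might infer from Step 1 that 53 can come only from a one-sided test. That goes too far: a non-directional between-group F test reaches 53 at a correlation of about 0.65, and a baseline-adjusted comparison passes through 53 somewhere between 0.42 and 0.5. What stands is that both routes need a correlation the article does not give. The F-test route is also parametric, whereas the section says non-parametric, and it tests the average of pre and post values, including a baseline that treatment cannot affect. From the stated inputs, the one-sided rank-sum test remains the simplest match, but it is still an inference about software settings that are not shown.

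**The 70% is not the power of the named analysis.** A reader might take it as the power of the Friedman or analysis-of-variance plan. It was not computed for those. It belongs to a two-group rank test with normal parent, and heavy ties on an ordinal rating would change it.

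**The hypothesis is directional.** A one-sided calculation would be consistent with it, in which case 53 is correctly calculated and the fault is undeclared sidedness. This stands as an explanation of how 53 may have arisen. It does not declare a one-sided test, and the tests named are non-directional. The full protocol may record the number of tails, but the article itself prints an α, a power and an n alongside tests that do not fit them at the usual two-sided level.

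**Conclusion.** The point holds in this form. From the stated inputs, 53 per group is exactly the one-sided 5% rank-sum answer (power 0.803), and none of the two-sided two-group calculations tried gives it; the two-sided requirement is 67. No one-sided test is declared, and the named tests are non-directional, so the stated 80% is not supported at a two-sided 5% level. For a two-sided 5% two-group rank test with normal parent, 53 per group gives about 70% power at d = 0.5 and 80% at about d = 0.56.

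The documents do not show that the sponsor deliberately used a one-sided test, nor that the number was miscalculated. The finding is that sidedness is undeclared and that the stated power does not fit the usual reading of the tests named. It does not bias the effect estimate. Whether 130 enrolments cover the expected drop-out is a separate question and is not used here.

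**What to change.** Choose one of two options.

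1. **Two-sided.** In Sample size, state that with 53 per group a two-sided 5% rank test has about 70% power at d = 0.5 and 80% at about d = 0.56.
2. **One-sided.** Declare a one-sided 5% level in both Sample size and Analysis, and name a directional between-group test that matches it. Friedman and the analysis-of-variance F test do not.

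In either case, state which G*Power test was used and any pre-post correlation assumed. If a repeated-measures calculation with a correlation near 0.65 was in fact the source, saying so and justifying the correlation would explain the 53.

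The cost is a few sentences. No extra enrolment is asked for. The two-sided option makes the stated power less favourable; the one-sided option makes the more lenient error rate visible.

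### Enrolling 130 with the expected 25 % drop-out leaves about 97 patients, 8 to 9 short of the 106 that the sample size calculation asks for

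*Protocol article*

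**What the plan says.** The Sample size section lists the inputs to a G*Power calculation: "a medium effect size" (d = 0.5) on the ADCS-CGIC, "a 1:1 allocation rate", a non-parametric analysis, and "an α-error of 0.05 and a power of 0.80". Whether the test is one- or two-sided is not said.

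The result is given as "Based on this calculation, each group shall include 53 patients". The next sentence sets recruitment: "The enrolment of 130 patients is planned, as a drop-out rate of" 25 %, a rate that "is expected based on the experience from the pilot study". The inflation formula is not shown. Nowhere else does the article give a different drop-out rate, a different target or a rule for replacing patients.

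**The concern.** The drop-out allowance exists so that the calculated number remains after losses. Here it falls short: at the expected loss, the trial finishes below its own requirement even if every planning assumption is met. The enrolment figure is the one that recruitment works to, so the shortfall carries straight into the trial. At stake is some power and a mis-stated evaluable number. Bias and type I error are not affected.

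**Working it through.** **Inputs, all from the Sample size section:** 53 per group; 130 enrolled; 25 % drop-out; d = 0.5; α 0.05; power 0.80; 1:1 allocation; non-parametric test.

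**Step 1. Reproduce 53 per group.** I took the noncentral-t power of a two-group comparison and scaled the group sizes by the Wilcoxon-Mann-Whitney efficiency 3/π.
- One-sided α 0.05: the smallest group size reaching 0.80 is 53, with power 0.803. This matches the protocol.
- Two-sided α 0.05: the smallest group size is 67, which does not match.

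The one-sided basis is therefore a reconstruction from the result. The article does not state it.

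**Step 2. Total required.** 2 × 53 = 106.

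**Step 3. Patients left under the plan.** 130 × (1 − 0.25) = 97.5, so about 97, or 49 and 48 per group. The shortfall is 106 − 97.5 = 8.5, that is 8 to 9 patients.

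**Step 4. Enrolment that would keep 106.** 106/(1 − 0.25) = 141.3, rounded up to 142 (71 per group). This is 142 − 130 = 12 more than planned.

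**Step 5. Loss that 130 can absorb.** (130 − 106)/130 = 24/130 = 18.5 %.

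**Step 6. Where 130 may come from.** Multiplying gives 106 × 1.25 = 132.5, close to 130 but not equal to it. Dividing gives 142, which is not close. So 130 is consistent with multiplying by 1.25 and rounding down.

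**Step 7. Effect on power.** Same method as step 1, assuming that drop-outs contribute no outcome:

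| Basis | Power at d = 0.5, 53/53 | Power at d = 0.5, 49/48 | Detectable d at 80 % power, 53/53 | Detectable d at 80 % power, 49/48 |
|---|---|---|---|---|
| One-sided (reproduces 53) | 0.803 | 0.771 | 0.50 | 0.52 |
| Two-sided | 0.702 | 0.663 | 0.56 | 0.59 |

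Within either row the drop-out shortfall costs 3 to 4 percentage points of power and 0.02 to 0.03 in detectable d.

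**The case against.** **Intention to treat.** The Analysis section puts the primary outcome on an intention-to-treat footing, and the article does not say whether a drop-out is someone who leaves the programme or someone without a post-intervention rating. If some drop-outs are still rated, more than 97 patients will be evaluable. This stands as a condition on the power figures. It does not rescue the sentence, because the section itself uses drop-out to justify enrolling more than 106.

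**The 25 % is a soft input.** It comes from a pilot of 18 patients, and 25 % of 18 is 4.5, not a whole number, so the rate is rounded or includes a margin. If 4 of 18 dropped out (an assumption, 22 %), 130 would leave 130 × 14/18 = 101. The gap is then within the uncertainty of the rate, and this bears on severity. But 101 is still below 106, and the plan's stated rate is 25 %.

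**Stronger readings that the documents do not support.**
- A reader might take it as established that the sponsor multiplied instead of divided. No formula is printed, 132.5 is not 130, and 130 could be a round recruitment target.
- A reader might say that the error takes power from 0.80 to 0.66, or detectable d from 0.50 to 0.59. That compares a one-sided start with a two-sided end. Two-sided power is already 0.70, and detectable d already 0.56, with the full 53 per group. The rest of that difference belongs to the unstated sidedness, a separate matter.

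**Conclusion.** The section is wrong as written: 53 per group, 130 enrolled and 25 % drop-out cannot all hold. The shortfall of 8 to 9 patients follows from the plan's own figures and needs no assumption beyond the stated drop-out rate.

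The power cost is conditional. It assumes that drop-outs have no post-intervention ADCS-CGIC rating, that d is 0.5, and that the rank-test approximation in the working applies. On those terms power is about 0.77 instead of 0.80 on the one-sided basis that reproduces 53, or 0.66 instead of 0.70 if the test is two-sided.

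Severity is moderate. The loss is small, the drop-out rate is itself uncertain, and the validity of the comparison is untouched.

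**What to change.** Correct the enrolment sentence in the Sample size section in one of two ways:
- State that 130 enrolled with 25 % loss leaves about 97 evaluable patients and about 77 % power at d = 0.5, on the same basis as the 53 per group.
- State that 130 preserves "each group shall include 53 patients" only if loss does not exceed 18.5 %.

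Either costs one sentence and a slightly less favourable figure, with no change to the conduct of the trial. If the sponsor prefers to keep 106 evaluable at 25 % loss, the matching enrolment is 142, at the cost of recruiting 12 more patients. Sidedness should be settled separately.
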